## Abstract

**Background:**

The Food Guide for the Brazilian Population relies on natural or minimally processed foods mainly of plant origin such as beans and rice with low oil, salt, and sugar content and limited consumption of ultraprocessed foods. Reduction of ultraprocessed foods improves diet quality and energy consumption.

**Objective:**

The goal of this study is to evaluate the effectiveness of an intervention for the treatment of obesity in children, with counseling based on the Brazilian Food Guide plus control of total energy intake.

**Methods:**

A parallel, randomized clinical trial will include children aged 7 to 12 years. Randomization will be performed in blocks of 10 individuals using computer-generated random sequence numbers. Both the control and intervention groups will participate in 6 standardized educational activities based on the 10 steps of the Brazilian Food Guide. These activities will be conducted at the University Hospital Toy Library, located in the pediatric outpatient clinic. For the intervention group, in addition to the educational activities, an individualized food plan based on the nutritional recommendations of the Brazilian Society of Pediatrics will be prescribed and discussed with the mothers and fathers. The primary outcome of the study will be variations in body mass index, and secondary outcomes will include analysis of insulin resistance, blood pressure, body fat percentage, and waist and neck circumference.

**Results:**

This project was funded by the National Council for Scientific and Technological Development in December 2017 (grant no 408333/2017-0). Recruitment began in August 2018 and by September 2019, we had enrolled the 101 participants. In addition to the patients referred by the national system of regulation, recruitment was made by medical outpatient referral and external indication. This is an ongoing study. We expect the results to be published in November 2020.

**Conclusions:**

At the end of the project, in case of a positive result, a protocol for the treatment of obesity based on the Brazilian Food Guide will be proposed to the Unified Health System. A successful method to reduce childhood obesity is expected.

**Trial Registration:**

Brazilian Registry of Clinical Trials RBR-3st5sn; http://www.ensaiosclinicos.gov.br/rg/RBR-3st5sn

**International Registered Report Identifier (IRRID):**

DERR1-10.2196/16170

## Introduction

The global prevalence of excessive weight among children aged 5 years and younger, which was 42 million in 2013, is expected to increase to 70 million in 2025 [1,2]. In Brazil, the increase in the prevalence of obesity over the past few decades has been higher among children aged 5 to 9 years compared with adolescents and adults, with an increase of approximately 6 times in the period from 1974 to 2009 [3]. During this period, Brazilian adolescents’ diets were low in vegetables and fruits with a high intake of sodium-rich food, sweets, and soft drinks [4-6].

Obesity before the onset of puberty increases the risk of adult type 2 diabetes, particularly if it continues until puberty or even later [7], indicating a window of opportunity to reduce obesity and related diseases later in life.

The World Health Organization (WHO) recommends interventions to control obesity in childhood. Accordingly, in 2014, the World Health Assembly adopted the Global Action Plan for the Prevention and Control of Noncommunicable Disease 2013-2020, which includes reducing global obesity rates among children, adolescents, and adults [8].

The 2014 Food Guide for the Brazilian Population [9] is a strategy for the implementation of the Adequate and Healthy Food promotion guideline that integrates the National Food and Nutrition Policy. The guide is intended for the population aged 2 years and older and classifies foods based on the degree of industrial processing. This classification, called the NOVA food classification system, comprises four groups: (1) unprocessed or minimally processed foods, (2) culinary ingredients, (3) processed foods, and (4) ultraprocessed foods [10,11].

High consumption of ultraprocessed foods has been associated with obesity, diabetes, and cardiovascular disease in different age groups [12-16]. Ultraprocessed foods are more energy-dense and contain higher levels of total fat, saturated fat, sugar, and salt and lower levels of protein and dietary fiber in comparison with unprocessed or minimally processed foods. In addition, they stimulate excessive consumption because of hyperpalatability, large portion sizes, and easy consumption. Therefore, they can be consumed as snacks anytime, anywhere and are often marketed intensively and persuasively. In a randomized trial with individuals eating ad libitum, the poor quality of a diet rich in ultraprocessed foods was also associated with greater energy intake when compared with a diet very low in ultraprocessed foods [17].

Obesity prevention reviews based on the promotion of positive eating behaviors have not achieved the desired impact [18,19], and trials for the treatment of obesity in the primary care setting are effective only when they include caloric restriction and parental involvement, as shown in the available literature reviews [20]. Reduction of energy intake associated with consumption of ultraprocessed foods may be improved by combining the NOVA classification with a food plan. Accordingly, a review of interventions to increase fruit and vegetable consumption among school children found improved targeted dietary behaviors; however, there were no effects on adiposity [21], suggesting that for the treatment of obesity, the amount of food consumed is also an important aspect to be considered. Thus, the aim of this project is to compare a Food Guide for the Brazilian Population–based intervention incorporating the NOVA classification of food with and without energy intake counseling. If effective, this proposal could guide the development of clinical protocols for primary care aimed at the treatment of obesity in children, a challenge in the Brazilian public health agenda.

## Methods

### Design and Study Population

Parents and Professionals for Healthy Eating–Pedro Ernesto University Hospital (PAPPAS HUPE) is a nonblind randomized clinical trial for the treatment of obesity in children referred by the National Regulatory System to the pediatric nutrition clinic of a university hospital located in the metropolitan region of the city of Rio de Janeiro, Brazil. Obese children aged 7 to 12 years are eligible to participate in the study. The exclusion criteria will be children diagnosed with genetic disorders associated with obesity (congenital leptin deficiency, Down syndrome, Prader-Willi syndrome) or endocrine disorder (hypothyroidism, Cushing syndrome) and patients already under nutritional monitoring or using weight loss medications. These data will be obtained through medical records and/or a questionnaire completed by parents.

The study will employ a parallel design with 2 comparison groups (Figure 1):

Control group that will receive monthly nutritional guidance based on the new Food Guide for the Brazilian Population [9];Intervention group that will receive monthly nutritional guidance based on the new Food Guide for the Brazilian Population and a home-based diet plan appropriate to the nutritional needs of the participants.

The protocol will follow the guidelines of the Consolidated Standards of Reporting Trials [22] and was registered prospectively with the Brazilian Registry of Clinical Trials [RBR-3st5sn].

**Figure 1 figure1:**
[figure not shown]
Consolidated Standards of Reporting Trials diagram. SISREG: Sistema Nacional de Regulação (National Regulation System).

### Ethics Approval and Consent to Participate

The project was approved by the Research Ethics Committee of the Pedro Ernesto University Hospital (CAAE: 87593118000005259). The parent or legal guardian of the child will be informed of the need to sign a consent form and assent according to Brazilian Resolution number 466/2012 on research involving human beings from the Health Council of the Ministry of Health to authorize the information provided by the population in a study, emphasizing privacy regarding identification of the content as well as the freedom to withdraw from the research at any time.

### Sample Size Calculation and Randomization Procedure

The sample size of 48 individuals per group was calculated based on a standard deviation of body mass index (BMI) equal to 3.0 and an expected difference of 1.72 BMI [23] units between the groups, considering a statistical power of 80% and significance level of 5%. We estimate that 5% of participants are likely to drop out of the study during the study follow-up period. To account for this, we have enrolled 101 participants in total.

After the recruitment phase, eligible participants will be randomly assigned to the control or intervention groups. The randomization, which is performed by the dietitian responsible for the trial, will be performed in a block of 10 subjects using a computer-generated sequence of random numbers. The allocation implementation mechanism will be numbered sequentially. Participants will be allocated to each group, and interventions will be promoted by trained nutritionists.

### Intervention

Both groups will participate in 6 monthly standardized educational activities based on the 10 steps of the Food Guide for the Brazilian Population, which will be carried out in the Hospital Toy Library. Recreational materials, audiovisual resources, and pedagogical support necessary to carry out the proposed educational practice, already available, are based on the Activity Notebook–Promotion of Adequate and Healthy Food–Infant Education, developed by the Ministry of Health in partnership with the University of the State of Rio de Janeiro for teachers and health professionals (Table 1) [24]. Activities will be conducted in groups of 10 children. To avoid contamination, activities for the control and intervention groups will be conducted on alternate days.

**Table 1 table1:** Description and objectives of the interventions.

Intervention	Description	Purpose of the activity
From food to meals	Addresses the following Food Guide steps: Step 1: make food in natura or consume minimally processed food Step 3: limit consumption of processed foods Step 4: avoid consumption of ultraprocessed foods	Enable participants to recognize food groups by degree of processing Facilitate reflection on the consumption of these food groups at home Help participants understand that usual meals should integrate fresh or minimally processed foods, enabling them to limit/avoid the consumption of processed and ultraprocessed foods
Fat, salt, and sugar	Addresses the following Food Guide step: Step 2: use oils, fats, salt, and sugar in small amounts by seasoning and cooking food	Make participants aware of the amount of fat, salt, and sugar present in food Help participants reflect on the amount of these ingredients in meals and on the possible consequences of high consumption
What a happy time	Addresses the following Food Guide steps: Step 5: eat with regularity and attention, in appropriate environments, and, whenever possible, with company Step 8: plan the use of time to give food the space it deserves	Help participants understand the concept and importance of commensality Help stimulate reflection about this practice
Going shopping	Addresses the following Food Guide step: Step 6: make purchases in places that offer varieties of food in natura or minimally processed foods	Help participants identify food sale locations close to where they live or study Make participants aware of the importance of shopping in places that offer varieties of food in natura or minimally processed foods Enable participants identify the characteristics that make places the most appropriate to buy their food
There is a child in the kitchen	Addresses the following Food Guide step: Step 7: develop, exercise, and share culinary skills	Encourage participants to engage in healthy meal preparation and develop and/or exercise their culinary skills Encourage participants to share the knowledge and recipes learned with family and friends
What do you have to eat and drink around here?	Addresses the following Food Guide steps: Step 9: give preference, when away from home, to places that serve meals made at the time and with food in natura or minimally processed foods Step 10: be critical about information, directions, and messages in commercial advertisements	Enable participants to make healthy choices when eating out Enable participants to critically analyze the advertisements and labels of food/products ready for consumption

Educational activities will also be held with parents addressing the same topics as those covered in the children’s workshops. Advice will include changes in family behavior related to food choices and purchases.

After the group activities, individual family consultations for the control and intervention groups will be held. In the control group, the counseling will reinforce lessons learned in educational activities, focusing on food quality. In the intervention group, a food plan will be prescribed for each participant based on nutritional recommendations of the Federal Council of Nutritionists and Brazilian Society of Pediatrics [25,26]. The plan will be reviewed monthly to match energy recommendations and weight change observed in the previous month.

In order to reduce follow-up losses and increase adherence to the study protocol, a telephone call in the week after the appointment will be made with those responsible for the children to evaluate potential difficulties in adhering to the guidelines provided. Those reporting difficulties in participating will be contacted weekly. This intervention description follows the template for the intervention description and replication checklist and guide [27].

### Data Collection

Those responsible for data collection will be trained to ensure a high quality of assessment. This training will be conducted with the objective of standardizing the measurement of data and ensuring reliability.

### Outcomes

The primary outcome of the study will be variations in BMI. The following secondary outcomes will be investigated: waist-to-height ratio (WHR), waist circumference (WC), neck circumference (NC), blood pressure, body fat percentage (BF%), and biochemical analysis of serum total cholesterol, low-density lipoprotein (LDL) cholesterol, high-density lipoprotein (HDL) cholesterol, triglycerides, glucose, and insulin resistance. Insulin resistance will be determined at the baseline and endpoint while the other biochemical analyses will be conducted at the baseline, midpoint, and endpoint. The remaining variables will be assessed at every consultation.

Body weight and BF% will be measured using a portable electronic scale (Tanita BC-558). Height will be checked in duplicate using an AlturaExata portable anthropometer (Belo Horizonte). Both measures will be collected with the children barefoot, wearing light clothes, with the arms extended from the side of the body, positioned by the Frankfurt horizontal plane [28,29]. To reduce potential BF% measurement errors, parents and children will be provided with guidelines regarding the intake of liquids, coffee, alcoholic beverages, laxatives, and diuretics prior to the anthropometric evaluation.

To measure WC and NC, a flexible and inelastic metric tape measuring 150 cm and a variation of 0.1 mm will be used. The WC will be measured with the tape placed horizontally at the midpoint between the lower edge of the last rib and the iliac crest [30]. The measurements will be performed with the tape firmly on the skin, without compression of the tissues. The evaluation will be made while standing with the abdomen relaxed and the arms extended out from the body. The WHR will be obtained by the quotient between WC and height, both in centimeters. The NC will be measured at the average neck height.

The classification of nutritional status will be based on BMI values for age, in z-scores, according to sex, based on the new curves proposed by WHO. BMI for age will be calculated using AnthroPlus 2007 software (WHO) [31], and the values obtained will be classified according to the recommended cutoff points for children aged 5 to 19 years: low weight (BMI for age <–2 z-scores), eutrophic (BMI for age ≥–2 and ≤+1 z-scores), overweight (BMI for age >+1 and ≤+2 z-scores), obese (BMI for age >+2 and <+3 z-scores), and severely obese (BMI for age >+3 z-scores). This classification will be performed at the baseline to confirm the inclusion criteria.

Blood pressure will be measured with the HEM-742 blood pressure monitor (Omron Healthcare Inc.), previously validated for use in adolescents [32]. Before taking the measure, it will be verified that the children do not have full bladders, have not taken medication and/or had coffee, and have not eaten up to 30 minutes before the procedure or engaged in physical exercise up to 1 hour before. The measurement will be performed on the right arm, at the level of the heart, supported on a table with a flat surface, with the palm facing up and the elbow slightly flexed. The individual should be seated with feet in contact with the floor or on a flat surface and remain at rest in that position for 5 minutes before the measurement [33]. Two measurements will be performed, with a minimum interval of 2 minutes, and the average of 2 measurements will be calculated. If the difference between the 2 measurements is equal to or greater than 5 mm Hg, a third measure will be taken.

Biochemical analysis of serum total cholesterol, LDL cholesterol, HDL cholesterol, triglycerides, and glucose will be determined at the baseline, midpoint, and endpoint. The biochemical analysis will be performed at the hospital’s central laboratory of clinical analyses. After 12 hours of fasting, 10 ml of blood from the left ventricle vein will be collected in vacutainer tubes. The samples will be divided into aliquots, placed in Eppendorf-type tubes, and stored at –80°C until use, when they will be processed and the serum analyzed in a biochemical analyzer (Cobas Integra 400 Plus/Cobas 6000, F Hoffman–La Roche Ltd) with a Roche cassette. Fasting glycemia will be determined by hexokinase, total cholesterol and triglycerides by the colorimetric method, and HDL cholesterol by the homogeneous method (F Hoffman–La Roche Ltd). LDL cholesterol will be calculated by the Friedewald et al [34] equation, recommended by the American Academy of Pediatrics: LDL cholesterol = total cholesterol – HDL cholesterol + triglyceride/5. Insulin will be measured in the hospital’s endocrinology laboratory with the Elecsys 2010 and Modular Analytics E170/Cobas (F Hoffman–La Roche Ltd) by means of a kit that uses the immunoassay method of electrochemiluminescence. The cutoff points used for the evaluation of the serum levels of total cholesterol and fractions will follow the recommendation of the Brazilian Guideline for Dyslipidemias and Prevention of Atherosclerosis [35], and for fasting glycemia the parameter will be that recommended by the American Diabetes Association [36]. Undesirable levels of total cholesterol and LDL cholesterol values equal to or above 170 mg/dL and 110 mg/dL, respectively, and glucose above 100 mg/dL will be considered.

Insulin resistance will be assessed by means of the homeostatic model assessment–insulin resistance (HOMA-IR) index (HOMA-IR = fasting glycemia [mmol/L] × fasting insulinemia [μU/L]/22.5). Values >2.5 will be indicative of insulin resistance.

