### Statistical Analysis

The rate of change of primary and secondary outcomes over time will be tested by intention-to-treat analysis based on mixed-effects models, which allow for consideration of incomplete follow-up data and take into account the correlation of repeated measures. Adequacy of the models will be checked graphically through the diagnosis of the residues [44]. The models will be adjusted for sexual maturation. For the analyses, SAS software version 9.4 (SAS Institute Inc) will be used.

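### As printed, the LDL cholesterol equation adds triglyceride/5 instead of subtracting it; applied literally, it overstates every LDL value by 0.4 × triglycerides and carries the triglyceride effect into the LDL comparison

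*Protocol article*

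**What the plan says.** All the relevant text is in the Methods of the protocol article.

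- **Outcome.** The Outcomes section lists the lipids and related measures among the secondary outcomes, with LDL and triglycerides as separate items: "low-density lipoprotein (LDL) cholesterol, high-density lipoprotein (HDL) cholesterol, triglycerides, glucose, and insulin resistance".
- **Measured inputs.** Three lipids are assayed: "total cholesterol and triglycerides by the colorimetric method, and HDL cholesterol by the homogeneous method".
- **Derived LDL.** LDL is not assayed: "LDL cholesterol will be calculated by the Friedewald et al [34] equation, recommended by the American Academy of Pediatrics". The equation then follows as "LDL cholesterol = total cholesterol – HDL cholesterol + triglyceride/5". It has no brackets around the last two terms, and no other form appears anywhere in the article.
- **Cutoffs.** The same section sets thresholds: "Undesirable levels of total cholesterol and LDL cholesterol values equal to or above 170 mg/dL and 110 mg/dL, respectively".
- **Timing and analysis.** The lipids "will be determined at the baseline, midpoint, and endpoint". The Statistical Analysis section states: "The rate of change of primary and secondary outcomes over time will be tested by intention-to-treat analysis based on mixed-effects models".

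**The concern.** Read by the ordinary order of operations, the printed rule takes HDL away from total cholesterol and then adds a fifth of the triglycerides. Total cholesterol minus HDL is everything that is not HDL. LDL is only part of that remainder, so a correction for triglycerides can only reduce it. The printed rule increases it.

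Because LDL is calculated, this equation defines the outcome. A laboratory or programmer who follows it would get a wrong LDL value for each child at all three time points. Three things are then at stake:

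- the reported LDL levels;
- the classification of children against 110 mg/dL;
- the between-arm comparison of LDL change.

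The last matters most for inference. The error is proportional to triglycerides, which are themselves an outcome that a diet plan may change, so it is not a constant that drops out of the comparison.

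**Working it through.** **Inputs.** From the protocol article: the printed equation, the LDL cutoff of 110 mg/dL and the three assessment times. The article gives no lipid values or expected lipid effects, so all total cholesterol (TC), HDL and TG figures below are assumptions, in mg/dL.

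**1. Internal consistency.** Rearranging the printed rule, LDL = TC – HDL + TG/5:

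LDL + HDL = TC + TG/5 > TC whenever TG > 0.

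Two fractions cannot add to more than their total, so the plus sign is wrong without recourse to any outside source. With a minus sign, LDL + HDL = TC – TG/5, which leaves TG/5 for the remaining fraction.

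**2. Size of the error in each value.**

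(TC – HDL + TG/5) – (TC – HDL – TG/5) = 2 × TG/5 = 0.4 × TG.

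| TG | Overstatement of LDL |
|---|---|
| 50 | 20 |
| 100 | 40 |
| 150 | 60 |
| 200 | 80 |

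**3. Effect on the 110 mg/dL cutoff, single profiles.**

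- TC 160, HDL 45, TG 100: printed 160 – 45 + 20 = 135; subtracted 160 – 45 – 20 = 95.
- TC 150, HDL 45, TG 100: printed 125; subtracted 85.

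Both profiles move from below the cutoff to above it. On a grid of TC (140, 150, 170) × HDL (40, 45, 50) × TG (50, 100, 150, 200) there are 36 profiles. With subtraction, 32 of them fall below 110. Of those 32, the printed form puts 30 at or above 110.

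**4. Effect on the cutoff, whole distribution.** Assume the subtracted-form LDL is normal with SD 25, and TG is log-normal with median 95 and log-SD 0.4, independent of LDL. The mean overstatement is 0.4 × 95 × exp(0.4²/2) = 41.2. The share at or above 110 is then:

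| Assumed LDL mean | Subtracted | As printed |
|---|---|---|
| 80 | 11.5% | 63.6% |
| 92 | 23.6% | 77.7% |
| 110 | 50.0% | 91.9% |

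**5. Effect on the between-arm comparison.** Let Δ be the between-arm difference in change. The printed form gives ΔTC – ΔHDL + ΔTG/5 and the subtracted form gives ΔTC – ΔHDL – ΔTG/5. The gap is 0.4 × ΔTG, whatever happens to TC and HDL.

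| ΔTC | ΔHDL | ΔTG | Printed ΔLDL | Subtracted ΔLDL | Gap |
|---|---|---|---|---|---|
| 0 | 0 | –10 | –2 | +2 | –4 |
| 0 | 0 | –20 | –4 | +4 | –8 |
| –4 | 0 | –20 | –8 | 0 | –8 |
| –5 | +1 | –20 | –10 | –2 | –8 |

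In the third row an LDL reduction of 8 mg/dL appears where there is none. In the first two rows the sign of the effect reverses.

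**The case against.** The strongest reply is that this is a misprint with no consequence for the data. The text names an established equation before writing it out, and lost brackets, as in TC – (HDL + TG/5), would explain the print exactly. The biochemical work is done in the hospital's central laboratory, and the article does not say who computes LDL or with what code. This stands in part: the document establishes a wrong rule, not wrong data, and the harm is conditional on the rule being applied as printed. It does not rescue the text, because the explicit formula is the only version the reader has.

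A second reply concerns the cutoff. The Statistical Analysis section describes rates of change and names no analysis of the proportion above 110 mg/dL. The percentages also depend on assumed lipid distributions and on independence of LDL and TG. That is fair. They are illustrations, shown here over a range of means, and the conclusion does not rest on them.

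Third, the 8 mg/dL figure is the gap between the two formulas. It shows as an 8 mg/dL LDL reduction only when LDL in the subtracted form is truly unchanged; other cases give other apparent effects with the same gap. This qualification is correct and is reflected in the table.

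Finally, LDL is one of many secondary outcomes, and any wrong value can be recovered from the measured lipids. That limits the damage and makes the repair easy. It is no reason to leave an outcome's defining formula wrong.

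**Conclusion.** The concern holds: the equation is wrong as written. It contradicts the fact that LDL and HDL are parts of total cholesterol, and it does not match the method the protocol names.

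If it is applied literally, each LDL value is too high by 0.4 × TG, and the between-arm LDL difference is shifted by 0.4 times the between-arm triglyceride difference. Both results are algebra and need no assumption. The mg/dL amounts and percentages depend on assumed lipid values, since the article reports none. Whether the trial's data are affected cannot be told from the document.

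The correction must be made before LDL is reported. The primary outcome (BMI), the sample size and the choice of model are not touched.

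**What to change.** 1. Replace the equation with: LDL cholesterol = total cholesterol – HDL cholesterol – triglycerides/5, and state that all terms are in mg/dL.
2. Confirm with the laboratory and in the SAS derivation, wherever LDL is computed, which form has been used.
3. If the plus sign was used, recompute LDL at baseline, midpoint and endpoint from the measured total cholesterol, HDL and triglycerides. Then redo the classification against 110 mg/dL and the LDL model.
4. As a routine data check, verify that LDL + HDL does not exceed total cholesterol in any record.

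The cost is a one-line correction, one check and, if needed, a re-run of one derived variable. No new data are required. The article describes the study as ongoing, so this can be done before results are reported.
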